**Methods:**

This randomized double-blind controlled study aims to recruit a total of 100 participants, consisting of 50 children aged 3–7 years with an EBP measure rated above the clinically significant range (T-score ≥ 60) (Eyberg Child Behavior Inventory-ECBI; Eyberg & Pincus, 1999) and their parents who are at least 18 years old. Participants are randomly assigned to the artificial intelligence-PCIT group (AI-PCIT) or the PCIT-sham biometric group. Outcome parameters include weekly ECBI and Pediatric Sleep Questionnaire (PSQ) as well as Child Behavior Checklist (CBCL) obtained weeks 1, 6, and 12 of the study. Two smartphone applications (Garmin connect and mEMA) and a wearable Garmin smartwatch are used collect the data to monitor step count, sleep, heart rate, and activity intensity. In the AI-PCIT group, the mEMA application will allow for the ecological momentary assessment (EMA) and will send behavioral alerts to the parent.

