## Methods

Our clinical trial is examining the AI-PCIT for treatment of externalizing behavioral problems in young children. Participants are recruited from Young Child Behavioral Clinic (YCBC) at Mayo Clinic in Rochester, MN, USA, and through advertisements at local pediatrics and family medicine clinics. Interested participants are initially provided information about the study and are scheduled for a consult in the Young Child Behavioral Clinic. The overall recruitment goal for the trial is *N* = 50 participants between ages of 3–7 years whose measure of EBP rated above the clinically significant range (T-score ≥ 60) (Eyberg Child Behavior Inventory-ECBI; Eyberg & Pincus, 1999) [3]. Participants are randomly assigned to AI-PCIT group or PCIT-sham biometric group. Each child is recruited with their parents who are at least 18 years old for a total recruitment of 100 participants. Participants are children aged 3–7 years old. They are of any gender, race, or ethnicity recruited from outpatient or inpatient care. Inclusion criteria include the patients’ ability to provide developmentally appropriate informed assent and legal guardians that are able to provide informed consent. Furthermore, the patient’s EBP severity must be rated above the clinically significant range (≥ 120; T-score ≥ 60) (Eyberg Child Behavior Inventory-ECBI; Eyberg & Pincus, 1999) [3]. The need for more intensive behavioral treatments such as an ER visit or hospitalization for behavioral dyscontrol will not be exclusionary or exit criteria. Participants must be fluent in the English language, have verbal abilities, and have the competency to consent based on ability to provide a spontaneous narrative description of the key elements of the study. Participants also require at least one smartphone and Internet access. Exclusion criteria for the PISTACHIo clinical trial include individuals who are unable to speak and understand English; patients who refuse or withdraw their consent, or those who are unable or unwilling to adhere to study procedures; and patients who do not have a smartphone and access to Internet connection. The study has the approval of the local institutional review board for human subject research protection (Mayo Clinic, Rochester, MN, USA).

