### Proposed analysis

This study is an exploratory clinical trial with the broad goals of demonstrating feasibility, producing pilot data, generating validate effect sizes, and informing future larger, multicenter trials. The level of significance will be set at *α* = 0.05 (two tailed), and to address multiple testing (where applicable), *p*-values will be adjusted using the false discovery rate. We estimated the sample size for this pilot study based on the hypothesis examining clinical outcome (ECBI) between the PCIT-AI group and PCIT-sham group (hypothesis 2a). We anticipate that a sample size of 50 participants per group (*N* = 100) achieves 70% power, at a 0.05 alpha level (two tailed) to detect an odds ratio of 2.0 favoring PCIT-AI with the proposed randomized design. To evaluate feasibility of the use of Garmin wearables, we will use descriptive statistics assessing the frequency of Garmin use in participants (70% or greater is defined as success for this hypothesis). A linear mixed model analysis of repeated measures will be used to evaluate the interaction effects of type of PCIT (AI informed or AI sham), time, and ECBI scores. A separate linear mixed model analysis will be used to evaluate the interaction effects of PCIT type (AI informed or AI sham), time, and PSQ scores with ECBI scores as a covariate. To evaluate concordance of sleep cycle data from children aged 3–7 as compared to parental rating scales of PSQ, we will use Spearman correlation coefficients and mixed linear regression models. Separate Spearman correlations and a mixed linear regression model will examine the relationship between biometric data from smartwatches (heart rate and movement) with weekly ECBI reports. Partial least-square regression networks will be used to derive multi-omic integration networks, and Spearman correlation will then be used to associate omics with physiological measures from smartwatches.

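### The stated 70% power for an odds ratio of 2.0 at 50 per group does not follow from the stated inputs, and the planned ECBI mixed model does not estimate an odds ratio

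*Protocol article*

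**What the plan says.** The sample size paragraph in Proposed analysis rests on the ECBI comparison between the AI and sham arms, which it labels hypothesis 2a. It begins "We anticipate that a sample size of 50 participants per group", gives the total as 100, and claims 70% power at a two-tailed 0.05 level "to detect an odds ratio of 2.0 favoring PCIT-AI with the proposed randomized design".

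The same section then names the ECBI analysis: "A linear mixed model analysis of repeated measures will be used to evaluate the interaction effects of type of PCIT", together with time and ECBI scores. The article names no logistic, ordinal or other model for ECBI that would yield an odds ratio. The ECBI cut-offs in Methods (120 or more; T-score 60 or more) are eligibility criteria and are not described as a response definition.

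On the number of children, the abstract describes the 100 participants as "consisting of 50 children aged 3–7 years" plus their parents. Methods agrees: "Each child is recruited with their parents who are at least 18 years old for a total recruitment of 100 participants".

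**The concern.** Alpha, sidedness, group size and odds ratio are all stated. The one input missing for a two-group binary comparison is the control rate, and power can be scanned over every value it could take. If no value comes near 70%, the figure cannot come from that comparison. Separately, an odds ratio and a mixed-model contrast in ECBI points are different quantities, so even a correct odds-ratio calculation would not tell a reader what the planned analysis can detect.

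This sentence is the article's only quantitative basis for its size. The article says that the trial will inform larger multicentre trials, and its Conclusion presents the trial as placed to judge superiority. A power figure that is too high would affect how a null ECBI result is read and how a later trial is sized.

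**Working it through.** **Inputs from Proposed analysis:** n = 50 per group, two-sided alpha 0.05 (z = 1.96), odds ratio 2.0, claimed power 70%. **Not stated, so scanned or assumed:** control rate, SD, within-child correlation.

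**1. One binary outcome per child.** With control rate p0, the AI-arm rate is p1 = 2·p0/(1 + p0). With pbar the mean of the two rates, power = Φ{[(p1 − p0)·√n − 1.96·√(2·pbar·(1 − pbar))] / √[p0(1 − p0) + p1(1 − p1)]}.

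The best case is p0 = 0.414, p1 = 0.586: (0.1716 × 7.071 − 1.96 × 0.7071)/0.6966 = −0.248, and Φ(−0.248) = 0.402.

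| Control rate | 0.1 | 0.2 | 0.3 | 0.4 | 0.5 | 0.6 | 0.7 |
|---|---|---|---|---|---|---|---|
| Power, 50 per group | 21% | 32% | 38% | 40% | 39% | 36% | 30% |

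The maximum over control rates from 0.01 to 0.985 is 40.2%, so the claimed 70% is not reproduced. At the best control rate, 104 per group gives 69.9% and 105 gives 70.3%. At 50 per group the smallest odds ratio with 70% power is about 2.75. One-sided 0.05, which is not what the article states, reaches 53%. At 25 per group the two-sided maximum is 22.4%.

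**2. Other readings at one time point, 50 per group, two-sided.**
- Ordinal (proportional odds, many-category limit): √(100 × 0.6931²/12) = 2.00; Φ(2.00 − 1.96) = 52%.
- Standardised difference: d = ln 2 × √3/π = 0.382; a t-test gives 47%. The more generous conversion ln 2/1.65 = 0.420 gives 56%.

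**3. Repeated ECBI scores, d = 0.382.** Power = Φ(d/√(2V/n) − 1.96), where V is the variance of the contrast in SD² units and ρ is an assumed exchangeable correlation. Example: for change to week 12 at ρ = 0.5, V = 1, so 0.382/√(2/50) = 1.91 and Φ(−0.05) = 48%.

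| Contrast | V | 50 per group, ρ = 0.5/0.6/0.7 | 25 per group, ρ = 0.5/0.6/0.7 |
|---|---|---|---|
| Change to week 12 | 2(1 − ρ) | 48/57/69% | 27/33/41% |
| Week 12, baseline-adjusted | 1 − ρ² | 60/67/76% | 34/39/47% |
| Mean of 12 weekly scores | (1 + 11ρ)/12 | 74/67/61% | 45/40/35% |
| Slope, random slopes (assumed SD 0.7 over the period) | (1 − ρ)/1.18 + 0.49 | 52/56/60% | 29/32/35% |
| Slope, random intercept only | (1 − ρ)/1.18 | 84/91/97% | 55/64/76% |
| Mean of 12, baseline-adjusted | (1 + 11ρ)/12 − ρ² | 94/95/98% | 71/73/80% |

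For the slope rows, time runs from 0 to 1 over 12 weekly scores, whose sum of squares is 1.18, and the slope difference reaches 0.382 SD at week 12.

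**4. Children per group.** Fifty children in two groups is 25 each if allocation is equal; the article does not state the ratio. For a simple two-mean comparison the standardised difference detectable with 70% power is (1.96 + 0.524) × √(2/n): 0.50 at n = 50 and 0.70 at n = 25.

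**The case against.** The strongest reply is that ECBI is collected weekly and analysed with repeated measures, so a single-time-point ceiling is the wrong yardstick. That stands in part. A reader might infer that 70% is impossible, or that 40% caps power under any analysis. The documents do not support this: 40% is the ceiling for one binary outcome per child, and several repeated-measures readings at 50 per group reach or pass 70%. The two most favourable (random-intercept slope and baseline-adjusted 12-week mean) can do so even at 25 per group. What the reply does not supply is a basis in the article, which gives no correlation, no conversion from odds ratio to score difference, and no repeated-measures premise for its figure.

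A second reply is that a condensed article need not print a control rate or response definition, and the reference to hypothesis 2a suggests a fuller document. That is accepted: the missing inputs are not held against the article. The binary result holds for every control rate, and the mismatch of scale lies between two statements the article does make.

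A third reply is that this is an exploratory pilot whose feasibility aim is assessed descriptively by wear time. That is also true, and it limits the consequence: no study procedure depends on this figure. But a pilot that publishes a power claim should publish one that follows from its inputs.

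One might also guess that 100 per group was entered by mistake, since that gives at most 68%. This is conjecture and nothing here rests on it.

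**Conclusion.** The point holds in a limited form. At 50 per group, two-sided 0.05 and an odds ratio of 2.0, a single binary ECBI comparison has at most about 40% power, and single-time-point ordinal or standardised-difference readings give about 47% to 52% (56% under the most generous conversion). The stated 70% is therefore unsupported by the stated inputs. It is also expressed on a scale that the planned linear mixed model does not estimate.

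A repeated-measures calculation could come near 70% at 50 per group: about 48% to 76% for week-12 contrasts or the unadjusted 12-week mean at ρ of 0.5 to 0.7. At about 25 children per group the same readings give about 27% to 47%. These ranges rest on assumed correlations, on d = 0.382, on equal allocation and on no attrition. The Discussion cites PCIT attrition of 25% to 69%, and Study procedures says withdrawn participants are neither replaced nor analysed, so the number analysed may be lower still.

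The head count of 50 per group against 50 children in all is a separate error. The binary figure fails even when 50 per group is granted.

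**What to change.** Replace the odds-ratio power statement in Proposed analysis with one of the following.

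- **If the mixed model is the intended test:** give the power, or the detectable AI-minus-sham difference in ECBI points, for that model at the actual number of children per group. State the target contrast (for example week 12, 12-week mean or slope), the SD, a range of within-child correlations and the allowance for attrition.
- **If a binary ECBI response is meant:** define it, give its expected control rate, name the analysis that yields the odds ratio and restate the power. For one binary outcome per child this is at most 40% at 50 per group and 22% at 25 per group.

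The cost is a short recalculation and one rewritten paragraph. The restated figure will probably be less favourable. For an exploratory pilot that can simply be reported, and no added enrolment is required.

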## Abstract

**Background:**

Emotional behavior problems (EBP) are the most common and persistent mental health issues in early childhood. Early intervention programs are crucial in helping children with EBP. Parent–child interaction therapy (PCIT) is an evidence-based therapy designed to address personal difficulties of parent–child dyads as well as reduce externalizing behaviors. In clinical practice, parents consistently struggle to provide accurate characterizations of EBP symptoms (number, timing of tantrums, precipitating events) even from the week before in their young children. The main aim of the study is to evaluate feasibility of the use of smartwatches in children aged 3–7 years with EBP.

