### Objectives

The overall objectives of this AI-PCIT treatment clinical trial are to evaluate feasibility of the use of wearables such smartwatches: in children aged 3–7 years with emotional behavioral problems (EBP). We hypothesize that children with EBP undergoing PCIT will adhere to and tolerate wearables (e.g., Garmin vivosmart4 smartwatch) by having at least 70% of enrolled patients being able to wear it 70% of their treatment period. This will be monitored by checking sleep, heart rate, and intensity of data obtained from Garmin watches. The study will also evaluate the effectiveness of AI-PCIT by comparing weekly behavioral treatment outcomes as compared with control group over a 12-week period. The study will also serve to track indirect behavioral measures on smartwatches (i.e., measurements of heart rate, intensity of activity) from young patients as compared to parental rating scales of ECBI (obtained weekly). These measures can then be used for target engagement biomarkers in future interventional trials. Finally, we will also collect whole blood from both child and parent to investigate exploratory analyses on biomarkers (e.g., C-reactive protein, metabolomics, exposomics) of response to PCIT.

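### Feasibility, the main aim, is judged on whether an observed percentage reaches 70%; with 50 children that benchmark needs its confidence interval and an all-enrolled denominator before it can support a conclusion about tolerability

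*Protocol article*

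**What the plan says.** The abstract of the protocol article puts feasibility first: "The main aim of the study is to evaluate feasibility of the use of smartwatches in children aged 3–7 years with EBP". The Objectives turn this into a hypothesis that children will adhere to and tolerate the watch, "by having at least 70% of enrolled patients being able to wear it 70% of their treatment period". The Proposed analysis section gives the test of that hypothesis: "descriptive statistics assessing the frequency of Garmin use in participants (70% or greater is defined as success for this hypothesis").

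Three other places bear on the point.

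- **Sample size.** It was derived for a different question: "We estimated the sample size for this pilot study based on the hypothesis examining clinical outcome (ECBI"). The abstract "aims to recruit a total of 100 participants, consisting of 50 children aged 3–7 years", while the power statement speaks of "We anticipate that a sample size of 50 participants per group".
- **Exclusions.** Study procedures says that participants withdrawn for non-adherence, or for meeting an exclusion criterion after consent, are neither replaced nor analysed.
- **Claim.** Proposed analysis calls the trial exploratory. The Conclusion nevertheless expects it to determine tolerability of smartwatches in this population.

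**The concern.** The rule compares a point estimate with 70% and stops there. Nothing in the article says how precisely 50 children can estimate the share who tolerate the watch, because the only design calculation concerns the behaviour score. A result of exactly 70% would be labelled a success for the main aim, and in the light of the Conclusion it could be reported as showing that at least 70% of such children tolerate the device. The data would support a much weaker statement.

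The denominator adds to this. If children withdrawn for not wearing the watch leave the analysis, the percentage is computed among those who largely did wear it. It then no longer answers the Objectives' question about enrolled patients.

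**Working it through.** **The plan's own figure.** No precision or error rate is stated for feasibility, so there is none to reproduce. The only design figure belongs to the behaviour-score hypothesis: it "achieves 70% power, at a 0.05 alpha level (two tailed") for an odds ratio of 2.0. No baseline rate is given, so I searched baseline rates from 1% to 98% for the highest power of a two-proportion comparison at 50 per arm. The maximum is at 41% versus 58.2%. The difference is 0.1716, the null standard error is √(2 × 0.496 × 0.504 / 50) = 0.100, and the alternative standard error is √((0.41 × 0.59 + 0.582 × 0.418) / 50) = 0.0985. Power = Φ((0.1716 − 1.96 × 0.100) / 0.0985) = Φ(−0.25) ≈ 40%. The 70% is not reproduced this way. Any gain from repeated measures is not described. The feasibility point does not depend on it.

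**Inputs for the feasibility rule.** n = 50 children (abstract and Methods) and threshold 70% (Proposed analysis), so success means at least 0.70 × 50 = 35 children. Assumption: the percentage is the share of children who meet the wear rule, as the Objectives word it.

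**Precision at the threshold.** The Clopper-Pearson limits for x of n are the 2.5% point of Beta(x, n − x + 1) and the 97.5% point of Beta(x + 1, n − x).

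| Observed | Exact 95% interval |
|---|---|
| 35/50 | 55.4% to 82.1% |
| 70/100 | 60.0% to 78.8% |

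For 35/50 the Wilson lower limit is 56.2%, the Wald lower limit 57.3% and the one-sided 95% exact lower limit 57.6%. The choice of method moves the bound by about two points. The second row covers the reading in which participants means 100 people.

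**How the rule behaves.** With X ~ Binomial(n, p), the chance of reaching the threshold is P(X ≥ 0.70n):

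| True rate | n = 50 (≥ 35) | n = 100 (≥ 70) |
|---|---|---|
| 55% | 2.2% | 0.2% |
| 60% | 9.6% | 2.5% |
| 65% | 28.0% | 17.3% |
| 69% | 50.8% | 46.2% |
| 70% | 56.9% | 54.9% |
| 75% | 83.7% | 89.6% |
| 80% | 96.9% | 99.4% |

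The rule rejects clearly poor feasibility and passes clearly good feasibility. It discriminates poorly just below 70%.

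**Effect of the denominator.** The Discussion cites attrition in this therapy of 25% to 69%. For illustration, suppose 25% of the 50 children were withdrawn and excluded: 50 × 0.75 = 37.5, say 38 remain. The threshold is then 27, since 27/38 = 71%. Against all enrolled children, if none of the withdrawn met the wear rule, 27/50 = 54%. The same trial passes on one denominator and falls well short on the other. How many would be withdrawn for non-adherence specifically is not stated, so this shows the direction and possible size, not a forecast.

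**The case against.** The case for leaving the rule alone has real weight.

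- The Objectives word the target as a share of enrolled patients. Read as a benchmark on this sample, 35 of 50 meets it by definition. That reading is tenable, so a reader who infers that the rule would declare a false hypothesis true goes further than the text: that holds only if the hypothesis is taken as a statement about a population rate. The hypothesis is about children with behaviour problems in this therapy, and the Conclusion speaks of tolerability in that group. This is why precision still matters to what is finally claimed.
- The article calls the trial exploratory and the analysis descriptive. Observed thresholds for going on are common in pilots, and this one passes only 2% of the time at a true 55% and 10% at a true 60%. Both points stand. It would be wrong to call the rule unsound as a benchmark.
- A statistical analysis plan that is not shown may add an interval. It may, and a missing interval alone would be no finding. But the article already defines success by the point estimate, and an interval reported elsewhere would not change that definition.
- The phrase on frequency of use could mean wear time and not the share of children, and the denominator could be 100. On the first reading the binomial figures do not apply. On the second they soften, as the tables show.

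A reader might also infer that success should require a lower confidence limit of at least 70%, which needs 42/50. The documents do not call for that. The bar would be reached only 31% of the time at a true 80% and 2% of the time at a true 70%, a severe standard for an exploratory trial that claims no error rate for feasibility.

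**Conclusion.** The point holds in a limited form. A 70% observed threshold is a reasonable go-on benchmark, but meeting it does not by itself establish that at least 70% of such children tolerate the watch. At 35/50 the data are compatible with true rates from about 55% to 82%, and at 70/100 from about 60% to 79%. A true rate of 65% would pass 28% of the time with 50 children and 17% with 100. The article fixes this badly in two respects: success on its main aim rests on the point estimate alone while its Conclusion promises more, and its exclusion of non-adherent participants conflicts with a target defined on enrolled patients.

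This rests on reading the percentage as the share of children meeting the wear rule and on treating children as independent. The change is worth making because it concerns the main aim and costs little. It does not undermine the design.

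**What to change.** In Proposed analysis:

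1. Keep 70% as the observed benchmark for going on to a larger study, and say that this is its role.
2. Compute it over all enrolled children, in line with the Objectives. Children withdrawn for non-adherence count as not meeting the wear rule, and Study procedures should state that its exclusion from analysis does not apply to this endpoint.
3. Report the proportion with its exact 95% confidence interval.
4. Word the feasibility conclusion from that interval. For example: 35 of 50 children met the wear rule, which is compatible with true rates from about 55% to 82%.

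No higher success bar is needed. The cost is a sentence or two, with no extra children or data. The downside is that the feasibility claim becomes less favourable: the interval will look wide, and the all-enrolled denominator can only lower or leave unchanged a percentage from which children not meeting the wear rule had been dropped.

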### Study procedures

The PISTACHIo clinical trial utilizes a randomized, double blind, design to compare the active PCIT-AI group and PCIT-sham (treatment as usual) group. The child and primary caretaker are fitted with Garmin watches that are required to be worn for a minimum of 70% of the days during their 12 weeks of treatment. In addition to this, we require the participants to wear the watch for at least 70% of every 24 h per the principal investigator’s discretion. Families are scheduled for PCIT treatment with PCIT-certified therapist in the Young Child Behavioral Clinic. Before the first PCIT treatment session, all participants are randomized into an active versus sham arm of the study. This is done by using a computer-generated list based on a stratified randomization scheme and using a permuted block method with a random number generator. The research assistant, research coordinator, and computer engineer who monitors Garmin apps are the only team members aware of which group the participant belongs to (active vs sham) [20]. Study investigators, clinical/cognitive raters, and participants are blind to the treatment condition. Parents in the AI-PCIT group are receiving targeted messages that instruct them on how to de-escalate their child when the Garmin device recognizes vital signs associated with a child’s tantrum. Parents in the PCIT-sham group receive random messages throughout the day with various relaxation strategies such as reminders to practice deep breathing with their child. The treatment is overseen by board-certified child and adolescent psychiatrist who is a Within-Agency PCIT Trainer.

Any participants withdrawn from the study if they were non-adherent to study procedures or met exclusion criteria at any point after the consent will not be replaced, and their data will not be used for analysis. Additionally, broken watches will be replaced, and therefore, the participant will not be excluded from the study.

The ongoing clinical trial study protocol conforms to the International Consolidated Standards of Reporting Trials (CONSORT) guidelines and is registered on Oct 14, 2021, in clinicaltrials.gov (ID: NCT05077722), an international clinical trial registry. See Fig. 1 depicting the PISTACHIo study workflow and timing for study procedures.

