### Smartwatch technology and momentary assessments

This study will use Garmin vivosmart4 smartwatches (previously used in IRB application 20–002,133 preliminary study) to monitor the step count, sleep quality, heart rate (resting and active), and activity rates (i.e., how often subject moves). These data are available with granularity of each minute and will be recorded through Fitabase for both parents and children. Furthermore, for those in the active PCIT-AI arm, the child’s watch will feed data into mEMA that will trigger a behavioral alert to be sent to the parent participant. Study staff will walk the parents/guardians through how to download the Garmin Connect and mEMA applications on their smartphones or tablets to allow for syncing of the data from the smartwatch to Fitabase or mEMA. Families who do not have their own smartphone or tablet will be provided with an iPod. We note that the choice of iPod for the study was made prior to Apple Inc.’s announcement of discontinuing the product’s manufacturing (May 10, 2022), but the iOS 16 will support the iPods until the study’s anticipated end date. Families will be guided to synchronize data at a minimum once at each PCIT appointment, yet ideally, every night. Garmin watches are waterproof, and participants will be encouraged to wear them at all times during the 12 weeks of treatment (minimum of 70% of the time, 70% of the days). The choice of 70% as a minimum threshold for compliance during the study allows for meaningful imputation of missing values [21]. Acoustic analysis of child vocalizations recorded during sessions will be analyzed using frequency and joint time–frequency modulation methods [22].

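### The feasibility success rule in the analysis section is a single 70% figure and does not match the two-level criterion in children that it is meant to test

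*Protocol article*

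**What the plan says.** The Abstract of the protocol article names feasibility of smartwatch use in children with emotional behavior problems as the main aim. Wear thresholds then appear in four places.

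- **Objectives.** The hypothesis concerns children: "We hypothesize that children with EBP undergoing PCIT will adhere to and tolerate wearables". It is judged by "having at least 70% of enrolled patients being able to wear it 70% of their treatment period". There are two thresholds, one for each child's wear and one for the share of children.
- **Study procedures.** "The child and primary caretaker are fitted with Garmin watches", and these are "required to be worn for a minimum of 70% of the days during their 12 weeks of treatment". Participants must also "wear the watch for at least 70% of every 24 h per the principal investigator’s discretion". The same section says that participants withdrawn as non-adherent are not replaced and that their data are left out of the analysis.
- **Smartwatch technology and momentary assessments.** The requirement is repeated as a "minimum of 70% of the time, 70% of the days".
- **Proposed analysis.** Feasibility is assessed descriptively by "assessing the frequency of Garmin use in participants (70% or greater is defined as success for this hypothesis").

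The opening of the Methods uses the word participants in two ways: for the 50 children, and for a total of 100 people made up of children and parents.

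**The concern.** The Proposed analysis section does state a decision rule for the main aim, and that rule is not the one in the hypothesis. The hypothesis asks how many children each reach 70%. The analysis asks whether a frequency of use reaches 70%, without saying whether this is an average over people, a share of people, or a share of days or hours, or whose watches count. The denominator is also unsettled: the hypothesis counts enrolled patients, while the withdrawal rule removes the data of those who did not adhere.

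At stake is the verdict on feasibility. If several readings survive and give different answers on the same data, the choice can be made after the wear data are seen. The within-day part of the wear requirement is also left to the principal investigator's discretion, which would matter if that requirement were used to classify a child as adherent.

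**Working it through.** The 70% is a chosen threshold, not a derived figure, so there is nothing to reproduce. The check is whether the same data give the same verdict under each reading.

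**Inputs.** 12 weeks of treatment (Study procedures) = 84 days = 84 × 24 = 2,016 h. 50 children (Methods, opening), and 50 parents if one caregiver per child is counted. Threshold 70% at every level. The wear patterns below are constructed illustrations, not trial data.

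**1. Share of children against average use.** The Objectives need 0.70 × 50 = 35 adherent children.
- 30 children at 100% and 20 at 30%: mean use = (30 × 100 + 20 × 30)/50 = 72%, a pass on average use. Share at 70% or more = 30/50 = 60%, a fail under the Objectives.
- The reverse also occurs. 35 children at 80% and 15 at 20%: mean use = (35 × 80 + 15 × 20)/50 = 62%, a fail on average use. Share = 35/50 = 70%, a pass under the Objectives.

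**2. Population, if participants is read as children plus parents.**
- 25 of 50 children and 45 of 50 parents compliant: (25 + 45)/100 = 70%, a pass, while 25/50 = 50% of children fails.
- If all 50 parents comply, 70 − 50 = 20 children (40%) are enough.

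**3. Unit of per-child wear.** The Objectives do not say whether 70% of the treatment period means time or days.
- Read as time: 0.70 × 2,016 = 1,411 h.
- Read as days that each meet the 70%-of-24-hours level: 0.70 × 84 = 58.8, so 59 days, each with 0.70 × 24 = 16.8 h. The least total wear that satisfies this is 59 × 16.8 = 991 h, and 991/2,016 = 49.2%. Such a child passes on days and fails on time.
- In the other direction, 50 days at 100% and 34 days at 60% give (50 + 34 × 0.60)/84 = 70.4/84 = 83.8% of time, a pass. Only 50/84 = 59.5% of days qualify, a fail.

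**4. Denominator.** Suppose that 30 of 50 enrolled children adhere and 8 are withdrawn for non-adherence. Counting all enrolled gives 30/50 = 60%, a fail. Leaving out the withdrawn gives 30/42 = 71.4%, a pass.

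**5. Precision.** At exactly 35 of 50 children, the Clopper-Pearson 95% interval is 55.4% to 82.1%.

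**The case against.** The best defence is that the sections fit together. Study procedures defines a valid day and the share of days, the Objectives apply this to at least 70% of children, and the Proposed analysis section is shorthand that points back to the hypothesis. A condensed article may leave the derivation to a fuller document, the trial is exploratory, feasibility is only described, and minute-level data would let every version be reported. Much of this is fair, and it lowers the weight of the point. But no section says that the parts fit together in this way, and a stated success rule that differs from its own hypothesis is more than omitted detail.

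Some stronger inferences are tempting, and the documents do not support them.

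- **That parents definitely count.** The Methods also use participants for children alone, and the hypothesis is about children. Pooling is a possible reading, not a stated one.
- **That the day-and-hour rule equals 49% of the period, with a shortfall of 420 h (1,411 − 991) for every child.** The 49% is a floor. It needs exactly 16.8 h on 59 days and none on the other 25, so 420 h is the largest possible gap. If 70% of every 24 h is taken literally for all days, total wear is at least 70% and there is no gap.
- **That Study procedures and the smartwatch section give competing success criteria.** They state wear requirements and a compliance minimum. Only the Objectives and the Proposed analysis section state success.
- **That the imputation rationale fails.** The protocol says "The choice of 70% as a minimum threshold for compliance during the study allows for meaningful imputation of missing values" and cites a source that is not at hand. The documents do not show which missing values are meant, or a limit that is exceeded.

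**Conclusion.** The mismatch is real and concerns the trial's main aim. The success rule in the Proposed analysis section carries one 70% threshold where the Objectives carry two, and it fixes neither the population nor the unit. The withdrawal rule conflicts with the enrolled denominator.

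The size depends on the data. In the constructed cases, a 72% average goes with 60% of children adherent, 70% of pooled participants with 50% of children, and 71% after exclusions with 60% of those enrolled. The first rests on reading the analysis rule as average use, the second on counting parents, and the third on applying the withdrawal rule to the feasibility analysis. If the sponsor intends none of these readings, one sentence settles the matter.

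This should be fixed, but it is a repairable conflict in wording and does not invalidate the trial. Neither unit is wrong in itself; a total-time unit would be a stricter preference, not a correction.

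**What to change.** In the Proposed analysis section, restate the criterion from the Objectives as the success rule: the proportion of enrolled children who each reach 70% wear, with success if this is at least 70%. In addition:

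- Report parents' wear separately and keep it out of the rule.
- Keep children withdrawn for non-adherence in the denominator as non-adherent, and state that the data exclusion in Study procedures does not apply to this endpoint.
- Name one unit for per-child wear, either total time or days that meet the 70%-of-24-hours level. Use it in the Objectives as well, and report the other as secondary.
- Apply the unit to the endpoint without case-by-case discretion.
- Give the proportion with an exact 95% confidence interval.

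The cost is a few sentences and one derived variable from minute-level data that the protocol already collects. The price to the sponsor is that the reported success rate may be lower, because non-wearers stay in and neither averaging nor parents can raise it.
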